#### Individually randomised RCT comparing active with opportunistic case finding

Within each practice randomised to the Targeted arm, each household will be further randomised to either active or opportunistic case finding. Thus in the event of multiple patients from the same household, they will therefore be allocated the same intervention group in order to avoid contamination. Allocation will be undertaken automatically by the research database as each practice list is uploaded.

### Outcomes

#### Primary outcomes

The primary outcomes are the percentage of the eligible population diagnosed as new COPD cases within the first year, and cost per additional case identified in each arm, comparing:Targeted case finding and routine practiceActive and opportunistic case finding

#### Secondary outcomes

Feasibility (process measures such as uptake and resource needs).Efficiency (number needed to target to identify one person likely to benefit).

### Diagnosing COPD

For the cluster part of the trial, patients in the routine arm may only be newly diagnosed with COPD during usual care and will be identified from GP records using the same method as that used to identify and exclude patients with a prior diagnosis of COPD in the initial search (Additional file 1: Appendix 1). The current NICE guidance is that patients with appropriate chronic respiratory symptoms must also meet spirometric criteria (FEV_1_/FVC < 0.7) [31]. Thus, in order to compare with routine care, our primary definition must be FEV_1_/FVC < 0.7 in the presence of respiratory symptoms. However this definition is controversial, and therefore, we propose also to use the “Lower Limit of Normal” (LLN) definition using the recently established GLI 2012 equations [41]. This requires that the post-bronchodilator FEV_1_/FVC ratio falls below the 5th percentile of the predicted values for patients’ age, height, sex and ethnicity. All patients must also report chronic respiratory symptoms. In sensitivity analyses we will explore other definitions such as use of different cut-offs for the LLN.

### Additional data collection

Data on the practices and patients will be collected at several stages during the trial:

#### Practice level information

Information on the characteristics of each of the participating practices will be collected, to include list size, number of eligible patients, number of existing COPD patients, deprivation score, rural/urban status, ethnicity profile, number of GPs, designated practice contacts and age profile of the practice.

#### Information on all eligible patients

At baseline, practices will provide an anonymised dataset on each of the eligible patients (in both routine practices and targeted arms) to allow comparison between the arms of the trial. To include: age, sex, ethnicity, smoking status, co-morbidities, health service use and reasons for exclusion.

At the end of the year, practices will also provide information on the number of consultations for each eligible patient, number of new cases of COPD identified outside or within the trial, whether patients have left the practice or have died, and among a sample, the number of flags remaining on the GP system to give an indication of the proportion of questionnaires distributed opportunistically.

### Statistical justification for sample size

As there are two primary outcomes, the significance level for multiple testing is adjusted so that in total (across both sample size calculations) there is a 5% significance level. The individually randomised component (outcome (b) below) comparing Active versus Opportunistic case finding requires far fewer patients for adequate power and is therefore given 0.25% significance level. The cluster component (a) is designated 4.75% significance level.

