#### (a) Targeted case finding versus Routine care cluster randomized design

Based on the authors’ modelling work [32], the proportion of new COPD cases detected in the Targeted group (averaged across both Active and Opportunistic arms) was assumed to be 3.15%. Based research by Simpson et al. [42], the proportion of new COPD cases detected in the Routine care group was assumed to be 0.75%. At the 4.75% significance level, with 80% power, this led to an unadjusted sample size required of 545 per group, in order to detect a difference of 2.4% between Targeted and Routine care arms.

We expect ~40% of a practice population to be age 40-79 yrs with 57% of these being ever smokers without a previous diagnosis of COPD [32]. Assuming therefore a conservative 1000 eligible patients per practice of average list size 6000, and adjusting for clustering of patients within practices, assuming a conservative ICC of 0.05 [43, 44] the sample size required was 27,768 per arm, equivalent to 28 practices per arm.

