#### (b) Targeted arm: Active versus opportunistic case finding

The following estimates are based on assumptions drawn from the authors’ previous modelling work [32]. We assume 50% allocated to the Active arm will respond; of the remaining patients 91% will visit their GP at least once in 12 months, 50% are offered the questionnaire and 90% of these will fill it out. In the Opportunistic arm we assume 50% are offered the questionnaire and of these 90% complete questionnaires (Figure 1). Of all responders to the questionnaire in both arms, we assume 48% are likely to report symptoms and be invited to spirometry, of which 70% will attend and 17% of these will have COPD. This leads to yield of 2.3% in the Opportunistic and 4.0% in the Active arms. At a 0.25% significance level, 3904 patients/arm are required to detect this difference with 90% power.

For the targeted case finding comparison, there will be 19,152 eligible in each arm, giving ample power for the primary comparison (based on above assumptions 448 new cases from Opportunistic arm and 771 from Active arm). This sample size provides additional power for secondary analyses and also allows more flexibility should the assumptions be more optimistic than anticipated.

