#### Primary analyses

There are two primary comparisons:

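### The fixed 4.75%/0.25% alpha split is valid, but weighted Holm from the same starting levels is never less powerful and costs nothing; the gain is small at the planning assumptions

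*Protocol article*

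**What the plan says.** Under Primary analyses the protocol article states that "There are two primary comparisons": (a) Targeted case finding versus routine care, randomised by practice, and (b) Active versus Opportunistic case finding, randomised by household within the Targeted arm.

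Statistical justification for sample size adjusts for the two so that "in total (across both sample size calculations) there is a 5% significance level". Comparison (b), judged to need a much smaller sample, "is therefore given 0.25% significance level. The cluster component (a) is designated 4.75% significance level". Each sample size is then worked out at its own level: (a) "At the 4.75% significance level, with 80% power", and (b) at 0.25% with 90% power, which needs 3904 per arm. With 19,152 expected per arm, (b) is described as "giving ample power for the primary comparison", and the same sentence ties the expected case counts to the assumptions set out before it.

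Neither the sample-size sections nor the primary and secondary analysis sections mention a step-down rule, a hierarchy, or any transfer of alpha from a rejected hypothesis to the other.

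**The concern.** As written, the levels are those of a weighted Bonferroni procedure. If (a) is won at 4.75%, (b) is still judged at 0.25%. If (b) is won at 0.25%, (a) is still judged at 4.75%. Alpha that could be passed on without breaching the 5% total is left unused.

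This bears mainly on (b). Its strict level is justified by its expected excess of power, and that depends on the planned difference of about 1.7 points. Much of that difference comes from assuming that Active-arm patients who did not return the postal questionnaire go on to complete an opportunistic one at the rate assumed for the Opportunistic arm. If that recapture largely failed, a real but smaller advantage of Active case finding could miss 0.25% and yet be well within reach at 5%.

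**Working it through.** **Inputs.** All are from the two sample-size subsections, (a) and (b). Sidedness is not stated; two-sided tests are assumed because they reproduce the plan's figures. Power below uses the unpooled normal formula, power = Φ(|p1 − p2|/SE − z), with SE² = [p1(1 − p1) + p2(1 − p2)]/n. Critical values are z = 3.023 (0.25%), 1.982 (4.75%) and 1.960 (5%).

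**The plan's own figures.**
- Alpha: 4.75% + 0.25% = 5.00%.
- (b): [0.023×0.977 + 0.040×0.960] × (3.023 + 1.282)² / 0.017² = 3903.3, so 3904 as stated.
- (a): the usual formulas give 525 (unpooled) or 529 (pooled) per group, close to the stated 545. The design effect is 1 + 999×0.05 = 50.95, and 545 × 50.95 = 27,768 as stated.
- Yields: cases per returned questionnaire are 0.48×0.70×0.17 = 0.05712. Opportunistic: 0.91×0.50×0.90 = 0.4095 return, giving 2.34%. Active: 0.50 + 0.50×0.4095 = 0.70475 return, giving 4.03%. These match the stated 2.3% and 4.0%.

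**Why Holm dominates.** Weighted Holm rejects (a) if p_a ≤ 0.0475, or (b) if p_b ≤ 0.0025. If either is rejected, it tests the other at 0.05. The first step is the fixed split itself, so no rejection is lost. As a closed test, it tests the joint null at 4.75% + 0.25% = 5% by Bonferroni and each single null at 5%. Family-wise error is therefore at most 5% whatever the dependence, including that from the shared Targeted-arm patients. Simulation under the joint null gave 4.76% to 4.98% over correlations from −0.9 to 0.9.

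**Gain at the planning assumptions.** With 28 practices of 1000, the effective n for (a) is 28,000/50.95 = 549.6. For 3.15% versus 0.75%, power is 81.8% at 4.75% and 82.3% at 5%. Power for (b) at 19,152 per arm is essentially 100% at either level.

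**Gain if recapture falls short (assumed scenarios).** Let r be the fraction of the planned recapture achieved. Active yield is (0.50 + 0.20475r) × 0.05712, and Targeted yield is the mean of the two arms. The 5% level reaches (b) through a win on (a), so, treating the tests as independent:

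Holm power (b) = power at 0.25% + power (a) at 4.75% × [power at 5% − power at 0.25%].

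The figure of 14,000 per arm is 28 practices × 1000, halved.

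| r | Active / Opportunistic | Targeted | Power (a) at 4.75% | n per arm | (b) at 0.25% | (b) at 5% | (b) under Holm |
|---|---|---|---|---|---|---|---|
| 0 | 2.86% / 2.34% | 2.60% | 66% | 19,152 | 56% | 89% | 78% |
| 0 | 2.86% / 2.34% | 2.60% | 66% | 14,000 | 38% | 78% | 64% |
| 0.25 | 3.15% / 2.34% | 2.74% | 71% | 19,152 | 97% | 99.8% | 99% |

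For the first row: 0.563 + 0.660 × (0.889 − 0.563) = 0.778.

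**The case against.** The strongest reply is that nothing here is wrong. The split sums to exactly 5%, the sample sizes reproduce at those levels, and a Holm design would also size each test at its starting level. The levels appear in the sample-size section of a condensed article, and a statistical analysis plan that is not shown may define the final testing rule. That stands: the article's silence does not show a decision to refuse recycling, and the point is an improvement, not a correction.

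Three stronger readings are tempting, and the documents support none of them.
- A reader might infer that (b) is under-powered. At the stated assumptions it is not: 19,152 per arm is nearly five times the 3904 required, and even a quarter of the assumed recapture leaves 97% power at 0.25%. Zero recapture is an extreme for which the article gives no evidence, since Active-arm records stay flagged until a questionnaire comes back.
- A reader might set 56% against 89% as the gain with no recapture. That treats 5% as always available to (b). The same shortfall lowers the Targeted yield to 2.60% and power for (a) to about 66%, so the attainable figure is about 78%.
- A reader might call the claim of ample power unqualified. The article already makes it conditional on its assumptions and says the large sample leaves room should they prove too optimistic.

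**Conclusion.** The fixed split is valid and does not exceed 5%, but weighted Holm dominates it. At the planning assumptions that is worth about half a percentage point of power for (a) and essentially nothing for (b). For (b) the gain is large only if the Active–Opportunistic difference is far below plan: about 22 points at 19,152 per arm and 26 points at 14,000 with no recapture, shrinking to about 2 points at 19,152 with a quarter of it.

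The power figures rest on two-sided tests, on independence of the two tests, on the plan's ICC of 0.05 with 1000 eligible patients per practice for (a), and on no clustering adjustment for (b), as in the plan's own calculation. Error control and the absence of any power loss need no assumption about dependence. Low severity.

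**What to change.** Keep the starting levels and add one sentence, fixed before the outcome data are analysed: (a) is tested at 4.75% and (b) at 0.25%, and if either is rejected at its own level the other is tested at 5%. If the statistical analysis plan already sets such a rule, nothing more is needed.

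No patients, data collection or design feature changes, and the sample sizes stand. The one cost is that confidence intervals matched to a stepwise procedure are slightly less simple to present than those matched to fixed levels.

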#### (a) Targeted case finding versus Routine care cluster randomized design

Based on the authors’ modelling work [32], the proportion of new COPD cases detected in the Targeted group (averaged across both Active and Opportunistic arms) was assumed to be 3.15%. Based research by Simpson et al. [42], the proportion of new COPD cases detected in the Routine care group was assumed to be 0.75%. At the 4.75% significance level, with 80% power, this led to an unadjusted sample size required of 545 per group, in order to detect a difference of 2.4% between Targeted and Routine care arms.

We expect ~40% of a practice population to be age 40-79 yrs with 57% of these being ever smokers without a previous diagnosis of COPD [32]. Assuming therefore a conservative 1000 eligible patients per practice of average list size 6000, and adjusting for clustering of patients within practices, assuming a conservative ICC of 0.05 [43, 44] the sample size required was 27,768 per arm, equivalent to 28 practices per arm.

#### (b) Targeted arm: Active versus opportunistic case finding

The following estimates are based on assumptions drawn from the authors’ previous modelling work [32]. We assume 50% allocated to the Active arm will respond; of the remaining patients 91% will visit their GP at least once in 12 months, 50% are offered the questionnaire and 90% of these will fill it out. In the Opportunistic arm we assume 50% are offered the questionnaire and of these 90% complete questionnaires (Figure 1). Of all responders to the questionnaire in both arms, we assume 48% are likely to report symptoms and be invited to spirometry, of which 70% will attend and 17% of these will have COPD. This leads to yield of 2.3% in the Opportunistic and 4.0% in the Active arms. At a 0.25% significance level, 3904 patients/arm are required to detect this difference with 90% power.

For the targeted case finding comparison, there will be 19,152 eligible in each arm, giving ample power for the primary comparison (based on above assumptions 448 new cases from Opportunistic arm and 771 from Active arm). This sample size provides additional power for secondary analyses and also allows more flexibility should the assumptions be more optimistic than anticipated.

### Statistics and data analyses

All statistical analyses will be undertaken in STATA version 13.

#### Primary analyses

There are two primary comparisons:

#### Targeted case finding vs Routine care (cluster design)

Baseline characteristics of patients and uptake rate at each stage will be described for each cluster, and compared across clusters to check for balance across groups. A multilevel logistic regression model will be used to model the probability of detecting a new case of COPD in the Targeted group compared with the Routine care group. Clustering of patients (by practice and household) will be accounted for using a multi-level structure. The data will also be modelled using a log-link and results from the logit-link and log-link models will be compared. OR and also RR and risk differences will be estimated [45, 46], as will the NNT (Number Needed to Target to identify one additional COPD case). The analysis will also adjust for variables used in the randomization (age, ethnicity, deprivation) which might affect probability of having COPD.

#### Within the targeted group, active case finding vs opportunistic case finding (individual patient design)

Baseline characteristics of patients will be compared for each arm (Active and Opportunistic) within each practice to check for balance. Clustering of patients within practices and households (if appropriate) will be accounted for using a multilevel logistic regression model. OR and also RR and risk differences will be estimated [45, 46], as will the NNT (Number Needed to Target to identify one additional COPD case). Between-practice heterogeneity in the effect of Active versus Opportunistic case finding will be examined, and if present, the range and variability of effects will be appropriately summarized.

#### Secondary analyses

In addition the following analyses are also of interest:

Multilevel logistic regression will be used to compare each of the two components of the Targeted arm with Routine careModels will also be extended to estimate the effect of practice-level covariates on rates of COPD detectionInteraction terms will also be included to assess whether patient-level factors such as age, sex, ethnicity, symptom profile and smoking history modify (interact with) treatment effects.The impact of clustering at the household level will be investigated in sensitivity analyses.

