#### Stage 1: respiratory questionnaire

##### Opportunistic

Patients in this arm will have their records flagged to prompt the consulting healthcare practitioner or receptionist to provide them with a brief screening questionnaire consisting of simple respiratory questions supplemented with basic socio-demographic and medical information (Additional file 1: Appendix 2). The questionnaire is based on validated questions, where available, and has been piloted. Patients who agree to take part will leave the questionnaire with the receptionist.

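### The planned treatment-by-symptom-profile interaction relies on questionnaire data that exist only after allocation, only in the Targeted arm and only for responders, so it cannot give a randomised subgroup effect

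*Protocol article*

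**What the plan says.** The Secondary analyses section says interaction terms will be included to assess "whether patient-level factors such as age, sex, ethnicity, symptom profile and smoking history modify (interact with) treatment effects". It lists symptom profile beside demographic factors, gives no source for it and excludes no comparison. The same list includes comparisons of Active and of Opportunistic with Routine care.

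Other sections show where symptom data could come from:

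- **Baseline extract, both cluster arms** (Information on all eligible patients): "To include: age, sex, ethnicity, smoking status, co-morbidities, health service use and reasons for exclusion". No respiratory symptoms are listed.
- **Allocation to Active or Opportunistic** (Individually randomised RCT): "Allocation will be undertaken automatically by the research database as each practice list is uploaded". This precedes any questionnaire.
- **Stage 1 in the Targeted arm** (Opportunistic): staff are prompted to "provide them with a brief screening questionnaire consisting of simple respiratory questions". Active patients are also sent it by post.
- **Routine care** (Diagnosing COPD): "patients in the routine arm may only be newly diagnosed with COPD during usual care and will be identified from GP records". No trial questionnaire is used.
- **Role of symptoms**: a positive answer is what leads to a spirometry invitation (Stage 2), and symptoms are part of the case definition, since "our primary definition must be FEV_1_/FVC < 0.7 in the presence of respiratory symptoms".

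**The concern.** An effect modifier in a randomised comparison should be fixed before allocation and measured alike in the arms compared. Questionnaire symptom profile meets neither condition. It is a product of the intervention, it exists only for patients who respond, and response is what the added postal mailing in the Active arm is meant to raise. It is also the gate between stage 1 and spirometry, so it lies on the path from allocation to diagnosis.

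At stake is the reading of a secondary result. A ratio near one within symptom strata could be taken to mean that Active case finding offers symptomatic smokers nothing beyond Opportunistic. It would in fact reflect the analysis having conditioned on the step at which the two approaches differ.

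**Working it through.** **1. Inputs**, all from sample size section (b):

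- Active: 50% respond; of the rest, 91% visit the GP, 50% of those are offered the questionnaire and 90% complete it.
- Opportunistic: 50% offered, 90% complete. The sentence does not repeat the 91% visit rate, but the stated yield needs it (step 2).
- Both arms: of responders, "we assume 48% are likely to report symptoms and be invited to spirometry"; 70% of those attend and 17% of attenders have COPD.
- 19,152 eligible patients per arm.

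**2. Reproducing the plan's figures**

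- Response, Active: 0.5 + 0.5 × 0.91 × 0.5 × 0.9 = 0.70475.
- Response, Opportunistic: 0.91 × 0.5 × 0.9 = 0.4095.
- Yield per responder: 0.48 × 0.70 × 0.17 = 0.05712.
- Yield, Active: 0.70475 × 0.05712 = 4.03%, or 771 of 19,152.
- Yield, Opportunistic: 0.4095 × 0.05712 = 2.34%, or 448 of 19,152.

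These match the stated 4.0% and 2.3%, and 771 and 448 cases. Without the 91%, Opportunistic would be 0.45 × 0.05712 = 2.57%, or 492 cases, so the plan's figures include it.

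**3. Who would have a symptom profile**

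| Arm | Share of eligible patients | Number of 19,152 |
|---|---|---|
| Active | 70.5% | about 13,497 |
| Opportunistic | 41.0% | about 7,843 |
| Routine care | none, from the data described | not applicable |

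With no symptom variable in Routine care, an interaction against that arm cannot be fitted.

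**4. Active versus Opportunistic on the plan's assumptions**

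| Patients analysed | Active | Opportunistic | Ratio |
|---|---|---|---|
| All randomised | 4.03% | 2.34% | 0.70475 / 0.4095 = 1.72 |
| Responders | 5.71% | 5.71% | 1.00 |
| Symptom-positive responders (0.70 × 0.17) | 11.9% | 11.9% | 1.00 |
| Symptom-negative responders, trial-found cases only | 0 | 0 | undefined |

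The whole assumed advantage of Active is the response ratio. Every later step is set equal in the two arms, so restricting to patients with a known symptom profile removes it.

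**5. If the later steps are not equal**

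The documents give no arm-specific rates. As an assumption, let the yield per symptom-positive responder in Opportunistic be 0.8 to 1.25 times the 11.9% in Active:

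- At 0.8 (9.52%): odds ratio (0.119/0.881) / (0.0952/0.9048) = 1.28.
- At 1.25 (14.875%): odds ratio (0.119/0.881) / (0.14875/0.85125) = 0.77.

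The contrast can then fall on either side of one. It would describe differences in who responds and in what happens after response, not the effect of offering one approach rather than the other.

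**The case against.** The strongest reply is that this is one item in an illustrative list of secondary analyses, in a condensed article. The article does not say where symptom profile comes from or which comparison it enters, and an analysis plan could settle both. Symptoms coded in GP records before allocation would be a legitimate modifier in all arms. This stands in part: such codes are not ruled out, so a reader should not infer that symptoms can never be known in Routine care. But the article lists no such data, and it names the variable without restriction.

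Four stronger readings are tempting and are not supported:

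- **That the analysis always erases the effect.** The ratio of 1.00 is exact only under the planning assumption of equal 48%, 70% and 17% rates. Otherwise the result is a biased contrast, not necessarily a null one. Nor do the figures measure an error in an interaction coefficient; they show what the stratum effects it would compare have become.
- **That symptom-negative responders can have no cases.** The zero covers trial-found cases only. Year-end data include new cases identified outside the trial. If symptom profile means type of symptom among positives, there is no structural zero, but conditioning on response remains.
- **That advice on whom to target first rests on this interaction.** The abstract's discussion attributes that advice to sensitivity analyses, and the economic section considers subgroups separately.
- **That smoking history shares the flaw.** Smoking status is in the baseline extract for all eligible patients. Only smoking detail taken solely from the questionnaire would be affected.

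**Conclusion.** The point holds for symptom profile as measured by the stage 1 questionnaire, the only symptom source the article describes. Against Routine care, for Targeted as a whole or for either component, the interaction cannot be estimated from the data described. For Active versus Opportunistic it conditions on a post-allocation step that allocation changes (70.5% versus 41.0% on the plan's assumptions), and so departs from the randomised comparison. The shift in yield ratio from 1.72 to 1.00 rests on the sample size section's equal later rates; the direction is open if those differ.

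The consequence is confined to a secondary analysis. The primary analyses do not use symptom profile as a modifier and are unaffected, as are interactions with age, sex, ethnicity and recorded smoking status. The change is worth making because the analysis as named would mislead if carried out, and correcting it is easy.

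**What to change.** In the Secondary analyses section:

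1. State that effect modifiers are limited to variables fixed before allocation and available in all arms compared: age, sex, ethnicity and smoking status from the practice record.
2. Remove questionnaire symptom profile from the interaction list. Admit symptoms as a modifier only if they are taken from GP records dated before allocation, in all compared arms.
3. Report yield by questionnaire symptom profile descriptively, among responders, and label it as not a randomised comparison.

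This takes about a sentence of text and no new data, unless the investigators choose to extract pre-allocation symptom codes. The cost is that there will be no randomised subgroup estimate by questionnaire symptoms, which the design cannot provide in any case.
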